## Abstract

**Background:**

Chronic low back pain (CLBP) is a disease with significant functional, emotional and social impact. Several interventions are proposed for its management and exercise is one of main, land-based or water-based. This study describes a randomized controlled trial that will analyze the effect of a combined aquatic and land-based exercise program compared to an aquatic-based program on pain, functional incapacity and quality of life in adults with CLBP. Additionally, it will analyze the effects of exercise cessation in the same outcomes.

**Methods and design:**

A blind randomized controlled trial will be developed with a 1:1 allocation ratio. Around 30 adults with mechanical CLBP will be randomly allocated in two groups. The experimental group (ALG) will complete an aquatic and land-based exercise program and control group (AG) will carry out only an aquatic program, both for 8 weeks. Participants will be assessed with Visual Analogue Scale, Oswestry Disability Index, Short-Form 36, Tampa Scale of Kinesiophobia-13 and Modified-Modified Schober Test, collected at baseline (M0), after 8 weeks (M1) and 4 weeks after the end of the intervention (M2).

**Discussion:**

This study may provide a relevant contribution to understand the potential effect of a combined land and aquatic exercise program on pain, functional disability, fear of movement, quality of life and lumbar mobility. The results may provide important information for CLBP management.

**Trial registration:**

This trial is registered with ClinicalTrials.gov (registration number: NCT06641570; date of registration: October 14, 2024).

## Introduction

Chronic low back pain (CLBP) is considered as “pain tension or stiffness localized below the costal margin and above the inferior gluteal folds”, lasting more than 12 weeks [1–3]. It can be distinguished in two main categories: specific, when the cause is attributed to a pathology or structural lesion and non-specific (accounts for about 90% of cases), when it is not possible to determine a recognizable known cause [3]. Low physical activity levels, obesity, smoking and high stress constitute risk factors for its occurrence [4].

This is one of the most frequent public health problems with a high prevalence in the world population [5]. According to GBD 2021 [3], CLBP in 2020 affected around 619 million people worldwide, and it is estimated that more than 80% of the population will have at least one episode of low back pain in their life [5]. The prevalence of CLBP is 4.2% in people aged between 24 and 39 years old and 19.6% between 20 and 59 years old, noting that women have CLBP more frequently than men [6]. Therefore, CLBP has a strong impact on functionality, well-being and quality of life, leading to limitations in social and work life of who suffers from this health condition, with economy implications and direct and indirect annual costs associated with health care resources usage [7–9].

These justify the need to study therapeutic strategies to manage this chronic condition. Some guidelines for the management of CLBP recommend physical exercise as a first-line treatment to reduce pain and disability, with programs duration superior than twenty hours for higher benefits, not mentioning the most appropriate type or intensity [10–12]. A systematic review with meta-analysis conducted by Hayden *et al*. [13] concluded that exercise can provide benefits in pain and disability caused by CLBP, compared to controls without treatment or with placebo intervention. Additionally, the same authors added that few studies report side effects associated with exercise.

On the other hand, prolonged periods of physical inactivity negatively impact the recovery from pain and functional disability caused by CLBP, so it is recommended that these individuals remain physically active [14]. Some authors suggest a variety of exercise types for managing CLBP, including aerobic exercise (from light to high intensity) [15,16], muscle strengthening exercises [17,18], and flexibility exercises [19]. Furthermore, Psycharakis *et al*. [20] highlight core stability exercises, as they recruit lumbar spine and pelvis stabilizing muscles. These exercises aim to counteract the decreased spine and pelvis neuromotor control and the muscle weakness of the abdominal and hip muscles observed in individuals with CLBP [21,22]. However, there is no consensus on the most suitable type of exercise, making it a controversial topic that requires further scientific research [23,24].

The reduction of lumbar spine stability due to decreased core muscle activity can lead to CLBP, with some studies indicating that activation exercises for the abdominal and spinal extensor muscles may play an important role in this condition management [25–27]. In turn, decreased lumbar spinal joint mobility and reduced flexibility in muscles such as the spinal extensors, hip flexors, and hamstrings may also contribute to CLBP persistence, justifying the inclusion of stretching exercises in exercise programs [26,28].

Another proposed modality is aquatic exercise, which utilizes the properties and characteristics of water for physical activity, aiming to reduce pain, strengthen muscles, and promote relaxation, among other benefits [29,30]. Thus, aquatic exercise is of particular interest, as the unique properties of water, such as buoyancy and hydrostatic pressure, reduce joint stress on the spine and other joints, and enhance balance, mobility, and pain control [29,31,32]. Additionally, the aquatic environment allows individuals to perform movements that are typically difficult or impossible on land [33]. Beyond this, continuous movement of the limbs against the resistance of the water leads to increased muscle strength and cardiovascular benefits [34–36]. A systematic review by Ma *et al*. [37] found that aquatic exercise programs were effective in reducing pain and improving quality of life and functional capacity in patients with CLBP, compared to other interventions or control groups with no intervention. Some authors argue that the buoyancy achieved during aquatic exercise can reduce the impact of gravity on the body, decreasing joint stress during exercise and pain [38–40]. Other researchers found that aquatic may be more beneficial than land-based programs in lumbar pain, health-related quality of life, and functional disability [41–43]. In contrast, Yalfani *et al*. [44] compared a Pilates exercise program performed in water with the same program conducted on land and found that both significantly reduced pain and dysfunction, with no significant differences between the programs. In light of these differences in the literature, no study has yet investigated whether there is an additional effect from combining land-based and water-based exercises on the same variables, compared to an exclusive water exercise program.

Moreover, few authors have investigated the effects of cessation of exercise [45,46]. Mujika & Padilla [46] argue that detraining can be divided into two study periods: short-term, less than 4 weeks, and long-term, more than 4 weeks. Therefore, Toraman & Ayceman [47] found that after 4 weeks of interruption following a 9-week aerobic, strength, and flexibility training program, conducted 3 times a week, participants showed a reduction in performance levels on various functional tests, standing out the Chair Sit and Reach, compared to the end of the intervention, although the changes were not statistically significant. Thus, the impact of aquatic exercise, core stability exercise, and trunk and lower limb stretching cessation on individuals with CLBP remains unclear.

This trial aims to assess the effect of a combined aquatic and land-based exercise program compared to an aquatic program on pain, functional disability, and quality of life in adults with CLBP. Secondary objectives include investigating the effects on lumbar mobility and fear of movement, as well as the impact of training cessation on these variables 4 weeks after the end of the intervention. We hypothesize that combined aquatic and land-based exercise decreases significantly pain, and functional disability, and increases quality of life in adults with CLBP.

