### Participants

The study sample will consist of both gender Portuguese participants, over 18 years, with CLBP lasting three months or longer and with an intensity of 3 or higher on the visual analogue scale (VAS) at rest. Individuals who refuse to participate or do not provide informed consent will be excluded, as well as those with pain radiating to the lower limb, recent pregnancy or childbirth (less than 8 weeks ago) [50], ongoing physical therapy treatments, severe rheumatological, neurological, neoplastic, cardiovascular diseases, or other conditions that could prevent full participation in the intervention, a history of spinal surgery, inflammatory, infectious, or malignant spinal diseases, and psychiatric disorders that may affect adherence and symptom assessment [41–43].

The sample will be randomly divided into two groups: the experimental group, which will undergo the aquatic and land-exercise program (ALG), and the control group, which will perform the aquatic-exercise program (AG).

The required sample size was calculated using the G*Power software (3.1.9.4; Heinrich Heine University Düsseldorf, DE), based on a study with 65 participants by Dundar *et al*. [42] and corroborated by other studies [51–53]. The aim was to detect differences in pain intensity (VAS) between the aquatic exercise program group and the control group (land exercise), with an effect size of 1.079, α=0.05, and a power of 80%. The total sample size needed to achieve the objective will be 30 participants (15 in each group).

Thus, the study should start with an additional 15% of the planned sample size for each group to account for potential dropouts and as well as adopt cognitive-behavioral strategies to reduce dropout rates, such as setting flexible and participant-driven goals or providing positive and individualized feedback [54,55].

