### Statistical analysis

An inspection of the data will be made for missing values or univariate outliers. A priori power analysis through ${\text{G}}^{*}$Power (3.1.9.7) [96] and ANOVA repeated measures, within-between interaction will be use to determine the required sample size considering the following input parameters: (effect size *f* = 0.4; α err prob = 0.05; statistical power = 0.95) [97]. Data analyses will be performed using SPSS Statistics version 29.0 (SPSS Inc., IBM Company, Chicago, Illinois, USA). Descriptive statistics (mean ± SD) will be performed for all variables in the analysis. Assuming data normality, a 2×3 within-between interaction factorial ANOVA will be applied for intra and inter group comparisons. To control for Type I errors, multiple comparisons will be adjusted using the Bonferroni correction (i.e., alpha level divided by the number of tests) as suggested by several authors (e.g., Ho, 2014) [98].The magnitude of the global effect size will be calculated using Cohen’s effect size. The Cohen’s *d* effect size is categorized according to the following criteria: *d* = < 0.20 (small), 0.21–0.79 (medium) and > 0.80 (large) [99–101]. Significance level set at ρ
≤ 0.05. Full statistical analysis and results are expected to be completed in May 2025.

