The study (RCT) with the most similar methodology was conducted with 66 participants (33 in each group) and aimed to examine the effect of an experimental aquatic and land-based exercise program compared to a control program of exclusively land-based (home-based) [43]. After two weeks of intervention, statistically significant differences were observed favoring the experimental intervention in pain: VAS at rest (ρ < 0.001), during exercise (ρ < 0.001), and overall in the lumbar spine (ρ < 0.001); in the ODI score (ρ = 0.045); and in the SF-36 domains of physical performance (ρ = 0.033), mental health (ρ = 0.021), pain (ρ = 0.014), and general health (ρ = 0.05). No statistically significant differences were found between the groups in the remaining domains of the SF-36 questionnaire or in the Modified-Modified Schober Test.

No study with a similar methodology has reported results for the TSK-13 questionnaire to date. Thus, it is challenging to predict the results of the study, as the methodologies differ and the sample sizes and intervention durations vary considerably among authors. It is not possible to project whether the group that will undertake the additional land-based exercise session will achieve better outcomes than the experimental group at the end of the intervention, in the studied variables. However, the variables most sensitive to the presented interventions appear to be pain, measured by VAS, functional disability measured by ODI, and some domains of the SF-36 related to pain and physical performance. These are likely to be the variables with the greatest variability at the end of the study. On the other hand, it is difficult to predict the trend of changes in the studied variables after 1 month of exercise cessation due to the lack of reference literature.

Thus, this study aims to provide implications for the practice and prescription of physical exercise and effective strategies that may contribute to potential benefits for individuals with LBP. Like all studies, this one will have some limitations: it will be impossible to fully control activities outside of the protocol, which may affect the studied variables either positively or negatively, and aquatic exercise limits the calculation of exercise intensity, which will be monitored only through perceived exertion.

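### The hypothesis names no comparator and does not match the comparative aim, and the analysis section does not tie it to the between-arm contrast

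*Protocol article*

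**What the plan says.** All references are to the protocol article.

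- **Introduction, aim.** The aim is comparative: "This trial aims to assess the effect of a combined aquatic and land-based exercise program compared to an aquatic program on pain", with disability and quality of life named alongside pain. The gap that motivates the trial is put the same way: "whether there is an additional effect from combining land-based and water-based exercises on the same variables, compared to an exclusive water exercise program".
- **Introduction, hypothesis.** The sentence that closes the same paragraph is: "We hypothesize that combined aquatic and land-based exercise decreases significantly pain, and functional disability, and increases quality of life in adults with CLBP". It mentions one programme and no comparator.
- **Statistical analysis.** The plan is that "a 2×3 within-between interaction factorial ANOVA will be applied for intra and inter group comparisons", and that "multiple comparisons will be adjusted using the Bonferroni correction (i.e., alpha level divided by the number of tests" (the number of tests is not given). No contrast is named as the one on which the hypothesis is judged.
- **Discussion.** On the expected result between arms: "It is not possible to project whether the group that will undertake the additional land-based exercise session will achieve better outcomes". No directional between-arm hypothesis therefore appears anywhere in the article.
- **Participants.** The sample size of 30 (15 per arm) was calculated for a between-group difference in VAS.

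**The concern.** The hypothesis defines what will count as a positive result. Taken at its word, a significant fall from M0 to M1 within ALG satisfies it, whatever happens in AG.

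That matters here because the control arm is active. The Intervention section gives the aquatic programme to both arms, and the Introduction cites a review that found such programmes effective for pain, quality of life and function. Improvement in ALG is therefore to be expected from the aquatic sessions alone. The Introduction also cites a trial of Pilates in water and on land in which both arms improved significantly and did not differ. If that pattern occurred here, the stated hypothesis would be met while the question the trial asks, whether land exercise adds anything, would have found no support.

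**Working it through.** **1. The plan's own sample size.** Inputs from Participants: d = 1.079, α = 0.05 (sidedness not stated), power 80%. For a two-sided two-sample t-test with n per arm, the non-centrality is d√(n/2) on 2n − 2 degrees of freedom.

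- n = 14: 1.079 × √7 = 2.855, critical t(26) = 2.056, power 78.5%.
- n = 15: 1.079 × √7.5 = 2.955, critical t(28) = 2.048, power 81.4%.

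The stated 15 per arm reproduces as a two-sided, between-group calculation. The number of participants was chosen for a comparison of arms, not for a pre-post test.

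**2. What a within-arm reading would give if land exercise adds nothing.** Inputs:

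- Completers in ALG: 15 (Participants).
- Common true fall in both arms: 20 mm. This is an assumption; the value is the minimal clinically important difference given for the VAS under Primary outcomes.
- SD of the M0 to M1 change: not in the article. Assumed 20, 25 or 30 mm.
- α: 0.05, and 0.05/3 if Bonferroni is applied to the three visit pairs. The divisor is also an assumption.

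For the paired t-test, dz = 20/SD and the non-centrality is dz√15 on 14 degrees of freedom. Critical values are 2.145 at 0.05 and 2.718 at 0.05/3.

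| Assumed SD of change | dz | dz√15 | P(significant) at 0.05 | P(significant) at 0.05/3 |
|---|---|---|---|---|
| 20 mm | 1.000 | 3.873 | 0.95 | 0.86 |
| 25 mm | 0.800 | 3.098 | 0.82 | 0.65 |
| 30 mm | 0.667 | 2.582 | 0.67 | 0.47 |

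**3. The same situation, judged between arms.** With identical true change in both arms, a two-sample t-test on the M0 to M1 change should reject 5% of the time. A simulation of 40,000 trials per SD, 15 per arm, gave 0.049, 0.049 and 0.050 for SD 20, 25 and 30 mm.

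**4. Reach of these figures.** The hypothesis joins pain, disability and quality of life. The probability that all three within-arm tests are significant cannot exceed the probability for VAS alone, so the table gives an upper bound for the joint statement.

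**The case against.** The strongest reply is that the sentence should be read with its paragraph. The aim, the research gap, the between-group sample size and the opening of the Discussion are all comparative, so the hypothesis may simply be an abbreviated comparative one. The planned model is a within-between interaction ANOVA, and the power statement in the same section is for that interaction, which tests differential change between arms. Most of this stands. A reader might infer that the trial has no controlled test, or that it is built to declare success on pre-post change; the documents do not support that. They never say that a within-arm result decides the hypothesis. What remains is that the one sentence defining success omits the comparator and nothing in the analysis section supplies it.

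Three further points limit the concern.

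- **Within-arm comparisons have a use.** A secondary objective is the effect of stopping exercise, and change from M1 to M2 is partly a within-arm question. A ban on all such tests would ignore it.
- **The Discussion sentence is a statement of equipoise, not an analysis rule.** It treats the difference between arms as open. Nor does the article say it would infer a difference from significance in one arm only, so that misuse is a risk and not a plan.
- **Regression to the mean.** Entry requires pain "with an intensity of 3 or higher on the visual analogue scale (VAS) at rest", and a reader might infer that selection on a high score produces a fall in ALG by itself. Selection is described as an earlier questionnaire step, and Data Collection places M0 as an evaluation after enrolment. If M0 is measured separately from screening, and correlations between visits are equal, the expected M0 to M1 fall from this source is about zero. No figure for it belongs in the argument.

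**Conclusion.** The point holds as a mis-stated hypothesis with no deciding contrast attached to it, in a trial whose design is otherwise set up for the right comparison. If the land sessions add nothing and both arms fall by 20 mm, a within-arm reading of VAS would confirm the hypothesis with probability 0.67 to 0.95 at 0.05 (0.47 to 0.86 at 0.05/3), against about 0.05 for the between-arm test. The range rests on an assumed SD of change of 30 down to 20 mm, an assumed common fall, and 15 completers in ALG; it is illustrative and is an upper bound for the three outcomes together. The sample size, the randomised comparison and the 2×3 model are unaffected. What changes is what the trial may claim.

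**What to change.** 1. **Introduction.** Restate the hypothesis as greater improvement in ALG than in AG at M1 in VAS, ODI and SF-36.
2. **Statistical analysis.** State that conclusions about the combination rest on the group-by-time contrast (the difference between arms in change), reported with its confidence interval.
3. **M0 to M1 within-arm changes.** Report them descriptively with confidence intervals, and not as evidence for the combination.
4. **M1 to M2 within-arm changes.** These may still be reported for the cessation objective. Any claim that the arms differ in loss of effect should rest on the between-arm contrast.

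The cost is a few sentences. The design, the number of participants and the data collection do not change. The authors give up a positive statement that would be easy to reach without any benefit from the land sessions.

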## Materials and methods

### Study design

This investigation will follow a quantitative model and a randomized controlled trial (RCT) study design, according to the Statement guidelines for standard protocol items in clinical trials (SPIRIT) and the Consolidated Standards of Reporting Trials (CONSORT) statement [48,49]. S1 Fig shows the SIPRIT checklist. This study protocol is registered in the Clinicaltrials.gov ID: NCT06641570 (date of registration: October 14, 2024).

### Participants

The study sample will consist of both gender Portuguese participants, over 18 years, with CLBP lasting three months or longer and with an intensity of 3 or higher on the visual analogue scale (VAS) at rest. Individuals who refuse to participate or do not provide informed consent will be excluded, as well as those with pain radiating to the lower limb, recent pregnancy or childbirth (less than 8 weeks ago) [50], ongoing physical therapy treatments, severe rheumatological, neurological, neoplastic, cardiovascular diseases, or other conditions that could prevent full participation in the intervention, a history of spinal surgery, inflammatory, infectious, or malignant spinal diseases, and psychiatric disorders that may affect adherence and symptom assessment [41–43].

The sample will be randomly divided into two groups: the experimental group, which will undergo the aquatic and land-exercise program (ALG), and the control group, which will perform the aquatic-exercise program (AG).

The required sample size was calculated using the G*Power software (3.1.9.4; Heinrich Heine University Düsseldorf, DE), based on a study with 65 participants by Dundar *et al*. [42] and corroborated by other studies [51–53]. The aim was to detect differences in pain intensity (VAS) between the aquatic exercise program group and the control group (land exercise), with an effect size of 1.079, α=0.05, and a power of 80%. The total sample size needed to achieve the objective will be 30 participants (15 in each group).

Thus, the study should start with an additional 15% of the planned sample size for each group to account for potential dropouts and as well as adopt cognitive-behavioral strategies to reduce dropout rates, such as setting flexible and participant-driven goals or providing positive and individualized feedback [54,55].

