#### Randomization and Blinding.

Participants who meet eligibility criteria will be given an alphanumeric code to maintain data confidentiality and anonymity. Participants will be randomly assigned to either ALG or AG, with a 1:1 allocation. Randomization will be performed by the principal investigator using a block randomization method generated by a computer program to ensure equal sample sizes in both groups. The block size will not be disclosed to maintain concealment. Participants will be informed of their group allocation (ALG or AG) via telephone contact. The principal investigator will not be actively involved in the intervention, data collection or data analysis. Randomization will only be known to the physiotherapists responsible for the intervention and the principal investigator. The examiner will evaluate participants before the intervention and after 8 weeks of intervention, ensuring blinding to group allocation, and participants will be asked not to disclose this information to the examiner. Each intervention will have a physiotherapist responsible for its execution, who will be instructed not to reveal participants’ group allocation to other research team members. Both data collector and data analyst will be unaware of the participants’ group distribution and will also be considered blinded. Only the principal investigator will have full knowledge of the entire research flow.

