## Discussion

This study will investigate and compare the effectiveness of a water-based and land-based exercise program versus a solely water-based program on pain levels, functional disability, quality of life, lumbar mobility, and fear of movement in adults with CLBP. Additionally, an effort will be made to assess the effect of the cessation of exercise on the mentioned variables, 4 weeks after the end of the intervention. A minimum of 15 participants per group is expected to ensure the calculated sample power. However, a higher number of participants should be ensured, as it is known that approximately 50% of participants drop out within the first six months due to personal characteristics, environmental factors, or issues with the programs [55]. On the other hand, in order to maintain the methodological quality of the study, according to the Physiotherapy Evidence Database (PEDro) Scale, the variables should be measured at the end in more than 85% of the participants who were initially randomized [102].

Previously, an author conducted a RCT with 12 participants (6 in the experimental group and 6 in the control group) in which the effect of an aquatic exercise program (experimental) was compared with that of a land-based program (control) on the level of pain and mobility of the lumbar spine [41]. At the end of the interventions (6 weeks), no statistically significant differences were observed in pain (VAS) (ρ=0.523), nor in the lumbar spine mobility test (Modified-Modified Schober Test) (ρ=0.56). Another author also studied in a RCT the differences between a group of participants who engaged in an aquatic exercise program (experimental) and a group who engaged in a land-based program (control) with 65 individuals with LBP (32 in the experimental group and 33 in the control group) [42]. After 4 weeks of intervention, statistically significant differences were observed favoring the experimental intervention in the ODI score (ρ < 0.001) and in the physical function (ρ < 0.001) and physical performance (ρ < 0.001) domains of the SF-36 questionnaire. No statistically significant differences were found between the groups in rest pain, pain during movement, or nocturnal pain (VAS), in lumbar mobility test (Modified-Modified Schober Test), or in the remaining domains of the SF-36 questionnaire.

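### The effect size of 1.079 behind N = 30 conflicts with the protocol's own account of the trial it is based on, and is for a different contrast, so the stated 80% power is unsupported

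*Protocol article*

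**What the plan says.** In the protocol article, Participants, the sample size is said to be based on a 65-participant trial and corroborated by references 51–53, for which no figures are given. The target is a difference in VAS pain "between the aquatic exercise program group and the control group (land exercise), with an effect size of 1.079", with "α=0.05, and a power of 80" per cent. The result is given as follows: "The total sample size needed to achieve the objective will be 30 participants (15 in each group"). A further 15% per group is added for dropout. Randomization and Blinding sets a 1:1 allocation.

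The Discussion describes the same 65-participant trial (same reference number; 32 aquatic, 33 land). It reports significant differences for the ODI and two SF-36 domains, but for pain it says: "No statistically significant differences were found between the groups in rest pain, pain during movement, or nocturnal pain (VAS"). The same section also states: "A minimum of 15 participants per group is expected to ensure the calculated sample power".

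The Discussion then turns to another trial: "The study (RCT) with the most similar methodology was conducted with 66 participants", 33 per group. That trial compared aquatic plus land exercise with home-based land exercise and reported VAS differences at p < 0.001 after two weeks. It is not named in the sample size paragraph as the source of the effect size.

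Statistical analysis gives a second a priori power specification, for a repeated-measures ANOVA within-between interaction: f = 0.4, alpha 0.05, power 0.95.

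**The concern.** The sample size paragraph and the Discussion describe one trial in two ways that do not fit together. A between-arm difference of more than one standard deviation in a 65-participant trial would be overwhelmingly significant, yet the Discussion says that none of its three VAS comparisons was.

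The contrast differs too. The input is for aquatic against land exercise. Here both arms receive the same twice-weekly aquatic programme, and the experimental arm adds one land session of 25 to 35 minutes a week. Nothing in the article argues that this increment should be worth 1.079 SD, and the Discussion says that it cannot be projected whether the arm with the extra session will do better.

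At stake is what the trial can be said to detect. If the true difference is moderate, a non-significant result is likely even though the land session helps, and a reader who relies on the stated 80% power would give that result too much weight.

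**Working it through.** **Inputs.** From Participants: d = 1.079, alpha = 0.05 (sidedness not stated), power 80%, 15 per group. From Randomization and Blinding: 1:1. From the Discussion: 32 v 33 in the source trial, with VAS not significant; 33 v 33 in the most similar trial, with VAS p < 0.001. From Outcome measures: VAS MCID 20 mm. No VAS standard deviation is given, so SDs of 15, 20 and 25 mm are assumed.

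**1. Reproduce N.** Two-sample t-test, two-sided 0.05, noncentral t with noncentrality d × √(n/2):
- n = 14 per arm: power 78.5%
- n = 15 per arm: noncentrality 1.079 × √7.5 = 2.95, power 81.4%

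So 15 per group (30 in total) reproduces. A one-sided test would need 12 per group and does not reproduce it.

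**2. Test the input against the Discussion.** Standard error of d in the source trial, approximately: √(1/32 + 1/33) = 0.2481.
- t at d = 1.079: 1.079 / 0.2481 = 4.35 on 63 df, two-sided p of about 0.00005.
- Largest observed |d| that is not significant: t(0.975, 63) × 0.2481 = 1.998 × 0.2481 = 0.496.
- Power of 32 v 33 for a true d of 1.079: 99%.

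Multiplicity does not explain the gap: a Bonferroni factor of 100 would still leave p of about 0.005.

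**3. What the most similar trial implies.** With 33 v 33 and p < 0.001, |d| is at least t(0.9995, 64) × √(2/33) = 3.449 × 0.2462 = 0.85. This is a floor, so 1.079 is not excluded there. That trial's comparator was home-based land exercise.

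**4. What 15 analysed per arm can detect** (two-sample t-test at one time point):

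| True difference | Power, 15 per arm | n per arm for 80% |
|---|---|---|
| 0.30 SD | 12.5% | 176 |
| 0.40 SD | 18.5% | 100 |
| 0.50 SD | 26% | 64 |
| 0.80 SD | 56% | 26 |
| 0.85 SD | 61% | – |
| 1.079 SD | 81.4% | 15 |

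The difference detectable with 80% power is 1.06 SD. In millimetres:
- SD 15 (assumed): 1.06 × 15 = 15.9 mm
- SD 20 (assumed): 1.06 × 20 = 21.2 mm
- SD 25 (assumed): 1.06 × 25 = 26.5 mm

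The detectable difference equals the 20 mm MCID at an SD of 20 / 1.06 = 18.9 mm. It is smaller than the MCID below that SD and larger above it.

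**5. With the dropout allowance.** 15 × 1.15 = 17.25, rounded up to 18 per arm. If all 18 were analysed, the detectable difference would be 0.96 SD, and power would be about 31% at 0.50 SD and 70% at 0.85 SD.

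**The case against.** The strongest reply is that the protocol's evidence does not all point to a small effect. The trial it calls most similar reported VAS differences at p < 0.001, which implies at least 0.85 SD. This stands as a reason not to treat 26% as the power of this trial. A reader might infer that figure from the non-significant source trial, but the documents do not support it: 0.50 SD is a ceiling on an observed effect, for aquatic against land exercise, and a non-significant observed effect does not fix the true one. Nor does the most similar trial rescue 1.079. Its control was home-based land exercise, so the aquatic programme was part of the difference between its arms, whereas here both arms receive it.

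Second, the ceiling of 0.50 assumes an unadjusted two-sided t-test; the Discussion names no test and the cited paper is not at hand. That limits what can be said about where 1.079 came from. It may be a within-group change, another measure or a figure from references 51–53. It does not restore the value as stated: the gap between p of about 0.00005 and non-significance on all three VAS measures is too wide for an ordinary choice of test to bridge, and references 51–53 come without figures.

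Third, the planned analysis is a 2×3 mixed ANOVA, so 1.06 SD from a t-test at one time point is not exactly the planned test's detectable difference. Use of baseline could lower it: with ANCOVA and an assumed correlation of 0.5, 1.06 × √(1 − 0.25) = 0.92 SD. That stands as a qualification, and it is also why the second power specification has to be reconciled.

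Finally, one might infer that the trial cannot detect the 20 mm MCID, or that the plan intends to read a null result as no added benefit. Neither is supported. The first depends on an SD that the article does not give, and no passage states the second. A rule tying the conclusion to whether the confidence interval excludes 20 mm would be a preference, not a correction.

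**Conclusion.** The concern holds as an unsupported input, not as an arithmetic error: 30 follows correctly from 1.079. As the Discussion describes the 65-participant trial, 1.079 cannot be its observed between-group VAS difference (t = 4.35, p of about 0.00005, against a non-significance ceiling near 0.50 SD under an unadjusted two-sided t-test). The value also belongs to a different contrast, and the corroborating references carry no figures. The claims of 80% power, and that 15 per group secures it, therefore lack a basis in the document.

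What can be said is conditional. Fifteen analysed per arm gives 80% power for about 1.06 SD, about 61% at 0.85 SD and about 26% at 0.5 SD, for a two-sample t-test at one time point. Which of these applies is not known from the article, and the origin of 1.079 cannot be determined from it.

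**What to change.** Keep N and change the text:

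1. In Participants, state where 1.079 comes from (study, outcome, contrast and how it was calculated), or drop its attribution as the between-group VAS difference of the 65-participant trial. If references 51–53 are kept as support, give their figures.
2. In the Discussion, remove the statement that 15 per group secures the calculated power.
3. State that 15 analysed per arm gives 80% power only for about 1.06 SD (two-sample t-test, one time point). Give this in millimetres with the SD used; for assumed SDs of 15, 20 and 25 mm it is about 16, 21 and 26.5 mm. Add the scenario powers: about 26% at 0.5 SD, and about 61% at 0.85 SD, the minimum implied by the most similar trial with a different comparator.
4. Reconcile this with the specification under Statistical analysis (f = 0.4, power 0.95), so that one calculation is named as the basis for N.
5. Say that a non-significant result will be reported with its 95% confidence interval and described as inconclusive for smaller effects.

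The cost is wording, with no extra participants. The downside is that the stated power becomes less favourable.
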